## 311 **9. Ethical requirements**

312 This clinical trial will be conducted in accordance with the Declaration of Helsinki and Good Clinical  
313 Practice (GCP).

### 314 **9.1 Ethics Committee**

315 Before the start of the clinical trial, the clinical trial protocol needs to be reviewed and approved by the  
316 ethics committee and signed for approval before it can be implemented. During the clinical trial, any  
317 modification of the clinical trial protocol and informed consent form must be approved by the ethics  
318 committee before it can be implemented.

### 319 **9.2 Informed Consent**

320 This clinical trial will provide all subjects with an informed consent form describing the study and  
321 provide sufficient information to allow subjects to make an informed decision about whether or not to  
322 participate in the study. This informed consent form will be submitted to the ethics committee for  
323 review and review together with the clinical trial process document. After the ethics committee has  
324 reviewed the informed consent form, subjects must sign the approved version of the informed consent  
325 form before entering any clinical trial. The informed consent form must be signed by the subjects  
326 themselves or their legal representatives, and the research professionals designated by the investigator  
327 will collect the informed consent form.

328

## 329 **10. Subject management**

330 During the treatment period, the subjects will be followed up by a special investigator, and if they feel  
331 unwell, they can contact the investigator at any time to ensure the safety of the patients to the greatest  
332 extent.

333 The subject's treatment compliance includes the subject's consent to participate in the study, willingness  
334 to receive the prescribed drug treatment, and willingness to collect blood samples and bone marrow  
335 specimens to evaluate efficacy and safety. Subjects may be excluded from the study due to lack of good  
336 compliance with treatment or follow-up at the discretion of the sponsor and investigator.

## 337 **11. Statistical Analysis Plan**

338 The Mann–Whitney tests, the chi-squared test, and Fisher's exact test were used to compare the AE  
339 between the MSC group and the control group. The competing risk model (Fine and Gray model) was  
340 used to estimate 2-year cumulative incidences and hazard ratios (HRs), with their 95% CIs, for severe  
341 cGVHD and cGVHD (competed by death and relapse) and leukemia relapse (competed by nonrelapse  
342 death). The cumulative incidence of grade II-IV aGVHD and grade III-IV aGVHD, the GRFS rate and  
343 the OS rate were estimated using Kaplan–Meier analysis and are expressed as percentages with 95%  
344 CIs. The Kaplan–Meier method, the log-rank test, and Cox proportional hazard models was used to  
345 compare the grade II-IV aGVHD and III-IV aGVHD, GRFS and OS curves between the two groups.  
346 All reported *P* values are two-sided. Statistical analyses were performed using STATA 17 (StataCorp.  
347 2021. Stata Statistical Software: Release 17. College Station, TX: StataCorp LLC)) and R (version  
348 4.4.2, R Foundation for Statistical Computing, Vienna, Austria).

349

350

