| Observation period       | (1) Real-time observation of the occurrence of acute and chronic GVHD after transplantation;
(2) Follow-up: relapse, death and HSCT related complication                                                                                                                                                                                                                                                                                                                                                                                                                                                                                              |
| Primary Endpoint         | Severe chronic GVHD                                                                                                                                                                                                                                                                                                                                                                                                                                                                                                                                                                                                                                      |
| Secondary Endpoint       | Chronic GVHD, acute GVHD, Overall survival (OS), GVHD-free and Relapse-free survival (GRFS).                                                                                                                                                                                                                                                                                                                                                                                                                                                                                                                                                             |

|                   |                                                                                            |
|-------------------|--------------------------------------------------------------------------------------------|
| Safety evaluation | Incidence of adverse events (AE) and severe AE during 45 days to 100 days after haplo-HSCT |
| Study period      | 2016.4-2022.2                                                                              |

29

30

31

32  
33  
34  
35  
36  
37  

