79 participate in regulating the growth of hematopoietic cells , and also have unique immunoregulatory  
80 properties. MSCs express moderate amounts of human leucocyte antigen (human leucocyte antigen ,  
81 HLA ) class I molecules , do not express HLA class II molecules , nor do they express FAS ligands and  
82 co-stimulatory molecules , such as B7-1 , B7-2 , CD40L, which can inhibit the Proliferative responses

of T cells in mixed lymphocyte cultures ( MLCs ) or mitogen stimulation. Animal experiments have found that MSCs from HLA-matched donors or " third parties " derived from expanded in vitro can prolong the survival time of allogeneic implantation into the skin after infusion into animals  , confirming that MSCs can play an immunosuppressive role in vivo.

The incidence of II-IV grade aGVHD after haploid hematopoietic stem cell transplantation is generally about 50%  , while the incidence of aGVHD in the treatment of refractory and recurrent hematological malignancies is only 24% after haploid hematopoietic stem cell transplantation combined with infusion of umbilical cord mesenchymal cells , suggesting that MSC combined infusion can prevent the occurrence of aGVHD  . In addition, our center proved for the first time internationally that the 2-year cumulative incidence of chronic GVHD after haplo -HSCT followed by sequential infusion of umbilical cord mesenchymal stromal cells (UC - MSCs) was 27.4%, which was significantly lower than 49.0% of the control group (P=0.021), showing that UC -MSCs can prevent the occurrence of cGVHD without increasing infection and tumor recurrence after transplantation  . The current studies on the prevention of GVHD by MSCs are all clinical studies on the prevention of aGVHD or cGVHD by MSCs alone. Based on the previous research, we plan to adopt the strategy of co-transplantation of UC-MSCs and HSCs and phased application of MSCs after transplantation to establish a safe and effective scheme that can prevent both aGVHD and cGVHD, and preliminarily elucidate its mechanism.

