## 144 **2. Purpose of the clinical trial**

145 To explore the efficacy and safety of umbilical cord-derived MSCs in preventing severe chronic  
146 graft-versus-host disease after haploid hematopoietic stem cell transplantation

147

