## 301 **8. Sample Size**

302 Sample-size estimates were based on the assumption of a log-rank test for the between-group  
303 comparison of the primary end point, the incidence of cGVHD. In the preliminary experiment, the  
304 cumulative incidence of severe cGVHD in the experimental and control group was 5.7% and 15%,  
305 respectively. We assumed 2 years for enrollment and 5 years for follow-up. A sample size of 142 total  
306 patients was calculated with a two-sided type II error of 0.05 and a statistical power of 90% for the

307 cumulative incidence of cGVHD. Considering the expected rate of loss to follow-up (10%), we decided  
308 to include 158 patients, with 79 patients in each arm. The sample size calculation was performed with  
309 PASS version 15 software (NCSS, Kaysville, UT).

310

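### Adverse events are compared between arms by significance tests only, with no effect estimate or confidence interval, although safety is a stated purpose of the trial

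*Combined protocol and SAP*

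**What the plan says.** Section 2 makes safety part of the trial's purpose: "To explore the efficacy and safety of umbilical cord-derived MSCs in preventing severe chronic" GVHD. The synopsis row on safety evaluation defines the measure: "Incidence of adverse events (AE) and severe AE during 45 days to 100 days after haplo-HSCT".

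Section 11 gives one sentence to analysing it. Besides Mann–Whitney tests, "the chi-squared test, and Fisher's exact test were used to compare the AE" between the two groups. No effect measure, interval, margin or bound for AEs follows.

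The other outcomes in section 11 are handled differently. The Fine and Gray model is "used to estimate 2-year cumulative incidences and hazard ratios (HRs), with their 95% CIs, for severe" chronic GVHD, any chronic GVHD and relapse. Acute GVHD, GRFS and OS are to be given as percentages with 95% intervals and compared by log-rank tests and Cox models.

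On error rates, section 11 says only "All reported *P* values are two-sided". Section 8 bases the sample size on chronic GVHD: "A sample size of 142 total" patients, raised to 158 (79 per arm) for 10% loss to follow-up, with a "two-sided type II error of 0.05 and a statistical power of 90% for the" chronic GVHD endpoint.

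**The concern.** A safety comparison should tell the reader how large an excess of harm the data allow and how large an excess they exclude. A p-value does neither. In a trial sized for another endpoint, a p-value above 0.05 can accompany a substantial observed excess, and it also looks the same whether the data are reassuring or merely sparse.

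If the plan is followed as written, the report would contain AE counts by arm and p-values. An added cell therapy that truly raised severe AEs by a relevant amount could then be summarised as showing no significant difference, with nothing beside that phrase to show what remains possible. The safety part of the trial's question would be tested but not quantified.

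**Working it through.** **Inputs from the documents.** 158 patients, 1:1, 79 per arm (sections 7 and 8); 142 before allowance for loss, or 71 per arm (section 8); two-sided p-values (section 11).

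**Inputs assumed.**
- Alpha of 0.05 for the AE tests. No alpha is stated for them; this is carried over from section 8, where the 0.05 is labelled a type II error and is read here as the significance level.
- Control AE rates of 1% to 60%, because the documents give none.
- A true excess of 10 percentage points, chosen for illustration. The documents name no excess to be excluded.

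**The plan's own figure.** 142 / (1 − 0.10) = 157.8, rounded up to 158, or 79 per arm. This step reproduces. No power for AEs is stated anywhere.

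**Chance of missing a 10-point excess.** With X₁ ~ Bin(n, p + 0.10) in the MSC arm and X₀ ~ Bin(n, p) in the control arm, the miss probability is the sum of P(X₁ = x₁)·P(X₀ = x₀) over all tables that are not significant. This was enumerated exactly for the uncorrected chi-squared test (|z| below 1.96, pooled variance) and for the two-sided Fisher test (p above 0.05).

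| Control rate | Chi-squared / Fisher, 79 per arm | Chi-squared / Fisher, 71 per arm |
|---|---|---|
| 1% | 17% / 31% | 22% / 38% |
| 2% | 25% / 39% | 30% / 46% |
| 5% | 42% / 53% | 47% / 59% |
| 10% | 57% / 66% | 61% / 69% |
| 20% | 69% / 75% | 72% / 78% |
| 30% | 73% / 79% | 76% / 82% |
| 40–50% | 77% / 81% | 77% / 82% |
| 60% | 73% / 79% | 76% / 82% |

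**A worked table.** Take 16/79 (20.3%) in the control arm and 24/79 (30.4%) in the MSC arm.
- Difference: 8/79 = 10.1 points.
- Pooled rate 40/158 = 0.253; z = 0.101 / √(0.253 × 0.747 × 2/79) = 1.46; chi-squared p ≈ 0.14.
- Fisher p = 0.20.
- Wilson 95% limits: control 12.9% to 30.4%; MSC 21.3% to 41.2%.
- Newcombe lower limit: 10.1 − √[(30.4 − 21.3)² + (30.4 − 20.3)²] ≈ −3 points.
- Newcombe upper limit: 10.1 + √[(41.2 − 30.4)² + (20.3 − 12.9)²] ≈ +23 points.

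Both tests are non-significant, yet the data allow an excess of up to about 23 points.

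**Width when the arms look the same.** The 95% half-width at equal rates p is 1.96 × √(2p(1 − p)/79). At p = 20% this is 1.96 × √(0.32/79) = 12.5 points. The same formula gives 9.4 points at 10%, 14.3 at 30% and 15.6 at 50%.

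**The case against.** The strongest case on the other side is that this is an exploratory phase II trial, and sizing such a trial on its efficacy endpoint is ordinary. The miss rates come from the sample size, not from the absence of an interval, and they would be the same with one. They also depend on the assumed control rate: at 1–2% the chi-squared test misses a 10-point excess only 17–25% of the time. A reader could compute a risk difference from the per-arm counts. All of this stands. It limits the point to how AEs are reported and means the miss rates must carry their assumptions.

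It does not remove the gap. Limited power is the reason to show an interval, and the plan provides one for every other outcome it analyses.

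Two stronger readings are tempting, but the documents do not support them.
- A reader might infer that the plan will call the treatment safe whenever p exceeds 0.05. No such rule is written. The safety measure is itself an incidence, relapse has a hazard ratio with an interval, OS has intervals and a Cox model, and section 6.7 suspends the trial for review after certain events within two weeks of infusion. That rule responds to single events and compares nothing between arms, but it is safety content.
- A reader might take the background's statement that the earlier study showed the cells "can prevent the occurrence of cGVHD without increasing infection and tumor recurrence after transplantation" as proof that non-significance was read as no harm. Section 1.1 gives a p-value only for chronic GVHD and nothing for infection. What lay behind the statement cannot be seen from these documents.

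**Conclusion.** The point holds as a gap in the planned analysis: for AEs, significance testing is the only between-arm analysis named, and no estimate or interval accompanies it. Because the trial was sized on chronic GVHD, a non-significant AE test would be weak evidence of no excess harm if AE rates are moderate or high. A 10-point excess would be missed more often than not by either test at control rates of 10–60%. At 5% it is close to even (42% by chi-squared, 53% by Fisher with 79 per arm), and at 1–2% the excess is more likely to be detected than missed. These figures rest on an assumed alpha of 0.05, assumed control rates and an illustrative 10-point excess. The trial's validity is not in question. This is a worthwhile, low-cost improvement to how its safety result is expressed.

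**What to change.** In section 11, add that for any AE, severe AE, serious AE and infection between day 45 and day 100 the report will give the number of patients with at least one event in each arm and the risk difference (MSC minus control) with a 95% confidence interval by the Newcombe or Miettinen–Nurminen method. Keep the chi-squared, Fisher and Mann–Whitney p-values as descriptive. State that a non-significant test will not be read as absence of harm, and that the safety statement will quote the upper confidence limit as the excess not excluded. This is a reporting rule, not a pass/fail criterion, since the plan sets no margin to judge against.

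The cost is a few sentences and one column in the AE table, with no new data or patients. The downside is a less favourable safety statement: with observed rates of 20% in both arms, it would have to say that an excess of up to about 12.5 points is not excluded. The change does not increase the trial's power for AEs.

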| Inclusion criteria       | (1) Patients diagnosed with acute leukemia who underwent haploid hematopoietic stem cell transplantation;
(2) Gender is not limited, age 18-60 years old;
(3) KPS score > 60 points, estimated survival time > 3 months;
(4) Patients without serious systemic organ dysfunction (a. creatinine <1.5mg/dl; b. albumin $\geq$ 2; c. cardiac ejection index > 55%; d. hemoglobin > 9g/dL, bilirubin element <2.0mg/dl);
(5) The patient has no other contraindications for hematopoietic stem cell transplantation;
(6) Voluntary test, informed consent.                                                                                   |
| Exclusion criteria       | (1) Severe cardiac, renal or hepatic insufficiency;
(2) Combined with other malignant tumors who need treatment;
(3) There are clinical symptoms of cerebral dysfunction or severe psychiatric disease, unable to understand or comply with the research protocol;
(4) Patients who cannot guarantee the completion of the necessary treatment plan and follow-up observation;
(5) Patients with severe acute allergic reactions;
(6) Clinically uncontrolled active infection;
(7) Patients who are participating in other clinical trials;
(8) The investigator believes that other reasons are not suitable for clinical trials. |
| Method of administration | 1. On the basis of routine GVHD prevention in the experimental group, UC-MSCs were reinfused 45 days after transplantation at a dose of $1 \times 10^6$ /kg per infusion; once every two weeks, a total of 4 times
2. Control group: routine GVHD prevention (Beijing program*) (MMF) 0.5g q12h -7d~90d, cyclosporine (CsA) 1.25mg/kg,; -1 day increment to 2.5mg/kg ; After the patient can tolerate orally, switch to 5 mg/kg orally, and the concentration is maintained at 200-300ng/ml; Slowly reduce the dose 180 days after transplantation; Methotrexate (MTX) 15mg/m  d1, 10mg/m  d3,6 ,11)                          |

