### 153 3.2 Criteria

#### 154 3.2.1 Diagnostic criteria and grading criteria for acute graft-versus-host disease:

155 Acute graft-versus-host disease: a syndrome that occurs within 100 days of allogeneic hematopoietic  
 156 stem cell transplantation and is characterized by rash, diarrhea, and cholestatic hepatitis. The diagnosis  
 157 of acute graft-versus-host disease in the upper gastrointestinal tract requires endoscopic findings.

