### 240     **6.3.2 Hematopoietic stem cell mobilization, collection and reinfusion**

241     The donors were given subcutaneous injection of recombinant human granulocyte colony-stimulating  
242     factor ( rhGCSF ) at  $10\text{ u g}/\text{kg} / \text{d}$  for 4 days, and peripheral blood stem cells (peripheral blood stem  
243     cells) were collected by a German Fresenius blood cell separator on d5 . blood stem cells , PBSC) . On  
244     day 6 , bone marrow collection was performed. After epidural anesthesia was performed, the donor was  
245     placed prone on the operating bed, and puncture was performed at different depths and multiple sites on  
246     the bilateral iliac ridges for collection; if it is estimated that more than 600ml of bone marrow fluid  
247     needs to be collected, the donor should be adjusted to the supine position, collected in bilateral anterior  
248     superior iliac spine puncture. If the donor and recipient ABO blood type is incompatible on the primary  
249     side, erythrocytes are removed by hydroxyethyl starch sedimentation; if the secondary side is  
250     incompatible, the bone marrow fluid needs to be centrifuged at  $4^{\circ}\text{C}$  at a low temperature, and then the  
251     plasma in the bone marrow fluid is removed with a plasma separator.

252     **6.4 Prevention of GVHD after haploid hematopoietic stem cell transplantation**

253     (1) Experimental group: On the basis of conventional GVHD prevention, UC-MSCs were infused 45  
254     days after transplantation at a dose of  $1 \times 10^6/\text{kg}$  with the interval of 14 days for 4 times.

255     (2) Control group: Beijing program for routine GVHD prevention (MMF) 0.5g q12h -7d~90d,  
256     cyclosporine (CsA) 1.25mg/kg, continuous intravenous drip; -1 day increment to 2.5mg/kg; After the  
257     patient can tolerate oral administration, it is changed to oral 5 mg/kg, and the concentration is  
258     maintained at 200-300 ng/ml; the dose is slowly reduced 180 days after transplantation; methotrexate  
259     (MTX) 15 mg/m^2 d1, 10 mg/m^2 d3, 6,11)

260     **6.5 Indicator observation**

261     (1) The incidence of severe chronic GVHD

262     (2) The incidence of II-IV acute GVHD, the incidence of chronic GVHD, OS, Post-transplant patient  
263     GRFS (GVHD-free and relapse-free survival)

264     **6.6 Therapeutic Monitoring Protocol**

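### Acute GVHD incidence is to be estimated by Kaplan-Meier, with no competing events, which modestly overstates it; the unstated time zero may also dilute the comparison between arms

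*Combined protocol and SAP*

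**What the plan says.** Section 11 puts acute GVHD in the same sentence as two survival endpoints. The sentence begins "The cumulative incidence of grade II-IV aGVHD and grade III-IV aGVHD, the GRFS rate and" and continues "the OS rate were estimated using Kaplan–Meier analysis and are expressed as percentages with 95" per cent confidence intervals. The next sentence uses Kaplan-Meier, the log-rank test and Cox models to "compare the grade II-IV aGVHD and III-IV aGVHD, GRFS and OS curves between the two groups". Neither sentence names a competing event or a censoring rule for acute GVHD.

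Just before this, the same section applies the Fine and Gray model to severe "cGVHD and cGVHD (competed by death and relapse) and leukemia relapse (competed by nonrelapse" death. The plan therefore recognises death and relapse as competing events for chronic GVHD.

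On timing:

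- Section 3.2.1 defines acute GVHD as "a syndrome that occurs within 100 days of allogeneic hematopoietic" transplantation.
- Section 6.4 states "On the basis of conventional GVHD prevention, UC-MSCs were infused 45" days after transplantation, "with the interval of 14 days for 4 times", that is, at about days 45, 59, 73 and 87. The synopsis and Section 5.1 also start at day 45.
- Section 7 does not say when patients are randomised, and Section 11 does not say when follow-up for acute GVHD begins.
- The background in Section 1.1 describes giving MSCs together with the graft. The treatment sections do not.

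**The concern.** Kaplan-Meier suits OS and GRFS, where death is itself an event. It does not suit the incidence of acute GVHD. Censoring a death treats the patient as still able to develop the disease, and one minus the curve then estimates a risk in a hypothetical population in which nobody dies first. That quantity is never below the true cumulative incidence. The excess grows with the number of competing events, so it can differ between arms. Acute and chronic GVHD would also be reported on different scales in the same paper.

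A second and separate question is what the comparison measures. If follow-up is counted from transplantation, acute GVHD before day 45 enters both arms before the treatment sections give any MSC. Those events carry no information on the effect of the infusions and pull the estimate toward no difference. Acute GVHD is a listed secondary endpoint, and the background states the aim of preventing it as well as chronic GVHD.

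**Working it through.** The documents give no expected incidence by arm, event count or power for acute GVHD, so there is no plan figure to reproduce.

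**Inputs from the documents.** Grade II-IV incidence of about 50% after haploidentical transplantation, and 24% in an earlier study with MSC co-infusion (Section 1.1); 79 patients per arm (Section 8); a 100-day window (Section 3.2.1); first infusion at day 45 (synopsis, Sections 5.1 and 6.4).

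**Assumptions, not in the documents.** The proportion *c* with a competing event before acute GVHD by day 100; the share of control-arm acute GVHD that precedes day 45; a hazard ratio of 0.50 after day 45.

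**Step 1: Kaplan-Meier against true incidence.** Let *p* be the true incidence at day 100. With constant cause-specific hazards, the total cumulative hazard is H = −ln(1 − p − c), the acute GVHD part is H₁ = H × p/(p + c), and one minus Kaplan-Meier is 1 − exp(−H₁).

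For p = 0.50 and c = 0.10: H = −ln(0.40) = 0.9163; H₁ = 0.9163 × 0.50/0.60 = 0.7636; 1 − exp(−0.7636) = 0.534.

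| Assumed c | 1 − KM, true 50% | 1 − KM, true 24% |
|---|---|---|
| 2% | 50.6% | 24.3% |
| 5% | 51.6% | 24.7% |
| 10% | 53.4% | 25.4% |
| 20% | 57.7% | 27.1% |

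If both arms truly had 50% but competing events were 2% in one and 10% in the other, the displayed percentages would differ by 53.4 − 50.6 = 2.8 points.

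**Step 2: early-onset disease.** Now let 90% of acute GVHD fall before day 45, with a constant competing hazard. At a true 50%, one minus Kaplan-Meier is 51.1% for c = 5% and 52.3% for c = 10%, against 51.6% and 53.4% above. Patients who already have acute GVHD cannot be censored by a later death.

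**Step 3: dilution, only if the clock starts at transplantation.** Control incidence is F = 0.50, and a share *s* of it precedes day 45. The hazard ratio is 1 before day 45 and 0.50 after. Competing events are ignored.

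- Early incidence in both arms: s × F.
- Control cumulative hazard after day 45: H_post = −ln[(1 − F)/(1 − sF)].
- MSC incidence: F_T = 1 − (1 − sF) × exp(−0.5 × H_post).
- Event-weighted average hazard ratio: 0.50 raised to the power w, where w is the share of all events (both arms) that occur after day 45.

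For s = 0.50: H_post = −ln(0.50/0.75) = 0.4055; F_T = 1 − 0.75 × exp(−0.2027) = 0.388; w = (0.250 + 0.138)/(0.500 + 0.388) = 0.437; average hazard ratio = 0.50^0.437 = 0.739.

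Approximate log-rank power (79 per arm, two-sided 0.05) uses an expected Z of 0.25 × D_post × ln 2 / √(0.25 × D) for the full window and √(0.25 × D_post) × ln 2 from day 45. D is the total number of events and D_post the number after day 45.

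| Share before day 45 | Average HR | Power, full window | Power, from day 45 |
|---|---|---|---|
| 0% | 0.500 | 78% | 78% |
| 25% | 0.615 | 51% | 66% |
| 50% | 0.739 | 24% | 48% |
| 75% | 0.869 | 9% | 27% |

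If time zero is day 45, the first row applies in the sense that there is no dilution, though the incidence still to come would be lower than 50%.

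**The case against.** The strongest reply is that little turns on this. Acute GVHD is secondary, and the primary endpoint, severe chronic GVHD, already has a competing-risk analysis. With 79 per arm, the 95% half-width around 50% is 1.96 × √(0.25/79), about 11 points, which is larger than any excess in Step 1. The two effects also do not peak together: heavy early onset, which maximises dilution, reduces the Kaplan-Meier excess. All of this stands, and it limits the weight of the point. It does not justify keeping an estimator that is biased in a known direction when the same paragraph already uses competing-risk methods.

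A reader might go further in four ways that the documents do not support.

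- *That relapse is censored for acute GVHD.* No rule says so. Sections 4.3 and 4.4 treat some disease changes, and relapse before infusion, as grounds for leaving observation or treatment, but they set no analysis rule. Censoring of deaths alone is enough for the bias.
- *That the analysis window includes days 0 to 45.* Section 3.2.1 is a diagnostic definition. The synopsis plans GVHD observation after transplantation, and Section 4.4 hints at enrolment before infusion, but the synopsis counts safety events from day 45. The documents do not settle time zero.
- *That the test between arms is invalid.* Log-rank and Cox with censoring at competing events compare cause-specific hazards and remain valid for that purpose. The Kaplan-Meier fault lies in the displayed percentages.
- *That the comparison could neither support nor refute prevention.* If both arms have the same prophylaxis until day 45, early events pull the estimate toward the null and cost power. A positive result would still be informative; a null result would be hard to read.

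**Conclusion.** The Kaplan-Meier point holds as a stated rule that is wrong for this endpoint. Followed as written, the plan overstates the incidence of grade II-IV and III-IV acute GVHD. At a true 50%, the excess is about 0.6 to 3.4 percentage points for an assumed 2% to 10% of competing events by day 100, and less if most acute GVHD is early. At a true 24%, it is about 0.3 to 1.4 points. The documents give no competing-event rates, so the direction is certain and the size is not.

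The dilution point is conditional. It applies only if follow-up starts before day 45, and its size rests on an assumed effect and an assumed timing of onset. What is established is that time zero is missing and that the answer could matter: under the assumptions above, the average hazard ratio lies anywhere from 0.50 (no dilution) to 0.869.

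Neither point touches the primary analysis. The change should be made, but the trial's main conclusion does not depend on it.

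**What to change.** 1. In Section 11, estimate grade II-IV and III-IV acute GVHD with the Aalen-Johansen cumulative incidence function, with death and relapse without acute GVHD as competing events, matching chronic GVHD. State the censoring rule. Keep the log-rank test and Cox model, labelled as cause-specific comparisons; Gray's test is optional. Keep Kaplan-Meier for OS and GRFS.
2. State time zero for acute GVHD and when randomisation takes place relative to transplantation and day 45.
3. Add a day-45 landmark comparison, the same in both arms, among patients alive, relapse-free and without prior grade II-IV acute GVHD. Tabulate earlier acute GVHD by arm separately.
4. Reconcile the background's mention of MSCs given with the graft with the day-45 start in the treatment sections. The landmark relies on the arms being treated alike until day 45.

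The cost is SAP wording and a few lines of code in R, which the plan already names. The downside is fewer events in the landmark comparison. At a 50% early share in Step 3, about 31 events remain (79 × 0.388) out of about 70 (79 × 0.888).
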